#### Debrief

After video recording has concluded, parents will be asked of their perceptions of the HRD, and their answers will be written by the primary researcher on a paper data collection form, as shown in Multimedia Appendix 2.

#### Data Management

Video recordings will be individually analyzed by 2 health professional researchers to determine the time it takes to apply the HRD to the thorax and the time from HRD placement to a steady HR display. Each researcher will review and record the HR from the HRD and PO or ECG at 2-second intervals for 3 minutes, providing approximately 90 HR notations per device per patient. For 50 newborns, the total number of HR annotations will be approximately 4500 data points. This will result in multiple HR data points to compare. To avoid human error in the annotation process, discrepancies in the HR of more than 5 beats per minute between the 2 researchers will lead to a reexamination of the video recordings until a consensus can be reached regarding the correct HR. The annotations from the 2 researchers will be averaged for the subsequent analyses.

Additionally, the HRD will record raw ECG signals for the duration of the device being in contact with the infant. Raw ECG data will be collected at 500 Hz sampling rate and transmitted to a research-dedicated laptop. The raw ECG and HR information from the HRD will be stored on different CSV files with a randomized identification number.

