**Conclusions:**

The study will compare the novel patent-pending 3D-printed dry electrode–based HRD’s real-time HR estimation techniques with the state-of-the-art clinical-grade ECG or PO monitors for HR accuracy and examines how fast the HRD provides reliable HR. The study will further provide recommendations and important improvements that can be made to implement the HRD for clinical applications, especially in neonatal resuscitation efforts. This work can be seen as a stepping stone in the development of robust dry-electrode single-lead ECG devices for HR estimations in the pediatric population.

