### Objectives

The overall aim of this research study is to evaluate a novel HRD that may enable timely and appropriate neonatal resuscitation. This study is being completed using a phased sequential user-centered approach. We completed the first phase of this research to determine end-user requirements and preferences for HR assessment in neonatal resuscitation. This phase resulted in the current design and features of the HRD.

The second phase outlines the creation of the HRD conceptual design and proof-of-concept prototype to be used in the final phase of feasibility mentioned in this study.

In the final phase, the focus of this proof-of-concept research study is to examine the functionality, speed, robustness, and reliability of the prototype HRD.

Specific research questions to be answered through this phase are the following:

How long does it take to place the HRD on an infant?Can the prototype HRD detect the HR of newborns?How fast can the prototype detect the HR of newborns?How accurate is the HR detection when compared to PO or ECG?

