#### Data Collection

The displayed HR from the HRD and the PO or ECG monitor will be video recorded for 3 minutes within the same video frame, as shown in Figure 1. Video recording will take place using a dedicated research digital camera mounted on a stand. Video recording will start once the infant is settled and the PO or ECG readings are stable. Stable readings are defined based on the device’s instructions on waiting for an appropriate amount of time after sensor placement for clinical HR determination. The HRD will then be placed on the infant’s chest until a consistent HR is displayed for 3 minutes, at which point video recording will start. After 3 minutes, the HRD will be removed, and then, the recording will be stopped. After the recording is completed, the entire HRD, including electrodes, will be wiped down with a surface disinfectant towelette (CaviWipe; Metrex). HRD device failure will be considered if no HR is displayed on the HRD within 60 seconds of application to the thorax.

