#### Data Analysis

HR and raw ECG data will be analyzed using MATLAB (the MathWorks). Infant demographics will be analyzed using summary statistics. Continuous variables will be expressed as mean (SD) values, and categorical variables will be expressed as numbers (percentages), unless otherwise stated. The HR from HRD will be compared to PO or ECG using a paired *t* test. The Bland-Altman method will be used to compare the HR derived from each device—the HRD and the PO or ECG monitor, used as reference. The correlation between devices will be assessed using Pearson *r* statistic. Data will be first analyzed using all data points available, and outliers will be defined as 20 beats per minute rate difference between the methods. These discrepancies will be further analyzed to find the likely reason for deviation, including reexamination of the video recordings.

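### The failure rule and the speed measure capture time to a displayed heart rate, not time to a reliable one, and two conflicting recording starts leave it open whether the onset is filmed

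*Protocol article*

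**What the plan says.** Objectives lists speed and accuracy as separate questions: "How fast can the prototype detect the HR of newborns" and "How accurate is the HR detection when compared to PO or ECG". Another question asks whether the prototype can detect heart rate at all. The Conclusions of the abstract join the two ideas and say the study "examines how fast the HRD provides reliable HR". Study Significance and Impact likewise describes the aim as the feasibility of getting accurate heart rates quickly.

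The operational definitions are these:

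- **Failure (Data Collection):** "HRD device failure will be considered if no HR is displayed on the HRD within 60 seconds of application to the thorax".
- **Speed (Data Management):** "the time from HRD placement to a steady HR display", read from video. "Video recordings will be individually analyzed by 2 health professional researchers" for this purpose.
- **Accuracy (Data Analysis):** "The Bland-Altman method will be used to compare the HR derived from each device", together with a paired t test and Pearson correlation. Differences of 20 beats per minute (bpm) between methods are treated as outliers and the video is re-examined.

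On when filming begins, Data Collection says two things. One sentence starts it when the infant is settled and the reference reading is stable, with the heart rate detector (HRD) placed after that. The next but one keeps the HRD on the chest "until a consistent HR is displayed for 3 minutes" and starts the recording at that point.

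**The concern.** A device meant for resuscitation is useful when it shows the right number quickly. Neither the failure rule nor the speed measure asks whether the number is right. If the HRD locks onto half or double the true rate and holds it, the display is steady, the clock stops and no failure is recorded. A numeric definition of steady, which the full protocol may contain, would not by itself change this, because steadiness is a property of the HRD display alone.

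At stake are two of the four research questions (can it detect, and how fast) and the abstract's statement about reliable heart rate. A short time to display could be read as a short time to a usable heart rate, which the defined measures do not establish.

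The conflict over the recording start decides whether the gap can be closed from the planned data. The reference value is described only as something read off the film. If filming begins after the HRD display has settled, no reference reading is described for the period that matters for speed.

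**Working it through.** **Step 1. The protocol's own counts.** Data Management gives readings every 2 seconds for 3 minutes. Readings per device per infant: 3 × 60 / 2 = 90. For 50 infants: 90 × 50 = 4500. Both match the article. It gives no power or precision calculation to reproduce.

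**Step 2. What each definition requires.**

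| Measure | Event | Uses the reference? | Uses time since placement? |
|---|---|---|---|
| Device failure | no display by 60 s | no | yes |
| Speed | steady display | no | yes |
| Agreement analyses | HRD minus reference | yes | no |
| Outlier flag | difference of 20 bpm | yes | no |

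No stated measure uses both the reference and time since placement. Time to a reliable heart rate needs both.

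**Step 3. Can the agreement analysis reveal an early error?** Assume the 90 readings start at contact and the display is wrong by *e* bpm for the first *t* seconds, then correct. Readings affected: *k* = *t*/2. Shift in that infant's mean difference: *e* × *k*/90.

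- *e* = 30, *t* = 20: *k* = 10, share 10/90 = 11%, shift 30 × 10/90 = 3.3 bpm.
- *e* = 20, *t* = 10: *k* = 5, shift 20 × 5/90 = 1.1 bpm.
- *e* = 20, *t* = 60: *k* = 30, shift 20 × 30/90 = 6.7 bpm.

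An early error is diluted by the later correct readings. The 20 bpm flag would mark these readings for review, but the flag changes neither the failure result nor the speed result.

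**Step 4. What a clean failure count shows.** With 0 failures in 50, the exact upper 95% bound is 1 − 0.05^(1/50) = 5.8% one-sided, or 1 − 0.025^(1/50) = 7.1% two-sided. This bounds the rate of no display. It puts no bound on the rate of wrong displays.

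**Step 5. Illustration of scale (assumed rates).** If 5%, 10% or 20% of infants had a display by 60 s that disagreed with the reference, then 0.05 × 50 = 2.5, 0.10 × 50 = 5 or 0.20 × 50 = 10 infants would count as non-failures. The document gives no basis for any of these rates.

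**Step 6. The two recording starts.**

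- *Start once the reference is stable, before placement.* HRD and reference are in one frame from contact. Time to first sustained agreement can be derived to about 2 s from the planned readings.
- *Start only after a consistent HRD display.* The onset is off film. The HRD stores its own heart rate and ECG, but no stored reference reading is described, so time to agreement cannot be derived from the described sources. Early errors also leave the accuracy data, because only settled displays are annotated.

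The second start also conflicts with Data Management, which reads application time and time to a steady display from the video. Both require placement to be on film.

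**The case against.** The strongest defence is that the article separates these concepts on purpose. Objectives and Study Design list detection, speed and accuracy as different things, and the speed question carries no reliability qualifier. For a first proof-of-concept device study, reporting time to display and agreement side by side is legitimate. The failure rule defines device failure only; it does not define detection success or a detection rate. A non-failure at 60 s with a steady display later is two measurements, not a contradiction. This stands, and it is why the existing measures should be kept.

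Gross miscounting would also not go unseen in annotated readings. Half counting differs from the true rate by HR/2, which exceeds 20 bpm whenever the rate is above 40 bpm, and double counting differs by the whole rate. Both would be flagged and the video re-examined. This stands for readings that are annotated, but the flag does not feed into failure or speed, and under the later recording start the early readings are not annotated.

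A reader might infer that the study cannot answer how fast the HRD gives a reliable heart rate. The document does not support that: if filming starts before placement, the paired 2-second readings contain the answer. A reader might also infer that the detection rate is overstated. That would follow only if early wrong displays occur, and the article has no data on how often they do.

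**Conclusion.** The point holds as a mismatch between what is measured and what the abstract and the significance section say is examined. As defined, failure and speed describe time to a display. Agreement is assessed separately and without reference to time since placement. The contradiction over the recording start is verifiable in the text and decides whether time to a reliable heart rate can be recovered at all.

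The size of any bias is unknown. The 2.5 to 10 of 50 infants rests entirely on assumed rates of 5% to 20%, and the shifts of 1.1 to 6.7 bpm rest on assumed early errors followed by correct readings over a full 90. They show the mechanism and are not estimates. The absence of a numeric rule for steady is not part of the finding, since an article may leave it to the full protocol. This is a worthwhile, inexpensive improvement and does not invalidate the design.

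**What to change.** 1. Reconcile Data Collection so that there is one recording start, with filming and the 2-second paired readings beginning at or before HRD contact with the thorax.
2. Keep no display by 60 s and time to a steady display as they stand.
3. Add time from thorax contact to first sustained agreement with the reference. State in advance the margin, how long agreement must last, and how infants who never reach it are counted.
4. Justify the margin as one for agreement between devices. The 5 bpm in Data Management is a tolerance between two people transcribing the same display and should not be adopted by default. Study Procedures itself notes that pulse oximetry and ECG monitors may show different rates.
5. Report infants with a display by 60 s that does not agree with the reference separately from infants with no display.

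The cost is wording in Data Collection, Data Management and Data Analysis, plus a slightly longer recording and annotation window if the later start was intended. The speed and detection results may look less favourable. If the added measure is declined, the abstract's statement about reliable heart rate should be narrowed to time to display.

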### Recruitment

All Infants admitted to the PPU after routine delivery, regardless of method, and all infants admitted to the NICU will be eligible if their clinical status is stable and not at high risk of deterioration. In total, 50 newborns will be recruited based on previous accepted research studies that focused on examining long-term neonatal ECG and HR monitoring applications using proof-of-concept novel ECG acquisition devices [14-19].

The two groups of infants are identified as follows:

Infants admitted to the PPU who are at least 24 hours of age and are undergoing routine critical congenital heart disease (CCHD) screening with PO.Infants admitted to the NICU who are routinely placed on 3-lead ECG or PO monitors.

Recruitment steps include the following:

Infants will be identified by a pediatrician for eligibility 5 days a week (Monday to Friday) between 8 AM and 8 PM. Recruitment on Saturday and Sunday will be done if feasible. Recruitment will happen on random days when a pediatrician is available and time permits.

Once an infant is identified based on eligibility (ie, inclusion and exclusion criteria), mentioned below, the pediatrician will ask the bedside nurse to ask the parents if they would be willing to speak to the pediatrician as shown in the recruitment script in Multimedia Appendix 1.

The pediatrician will then meet the parents in a face-to-face meeting to discuss the study, provide the written consent form, and potentially obtain consent. The parents will be given at least 15 minutes to review the consent form prior to being asked to sign it. When the parents are not available at the bedside, the pediatrician will inquire the nurse about a suitable time for the parents to meet. The infants will not be under the care of the researcher pediatrician as their primary admitting health practitioner to avoid a conflict of interest.

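### The paired t test, Bland-Altman and Pearson analyses are set on about 4500 two-second readings with no allowance for 50 infants giving about 90 each, so the t test p-value is invalid and any intervals would be too narrow.

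*Protocol article*

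**What the plan says.** All of this is in the protocol article.

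- **Sample.** Recruitment: "In total, 50 newborns will be recruited based on previous accepted research studies". The number rests on precedent, not on a calculation.
- **Readings.** Data Management sets the schedule: "Each researcher will review and record the HR from the HRD and PO or ECG at 2-second intervals for 3 minutes". The yield from each infant is put this way: "providing approximately 90 HR notations per device per patient". The total over the whole sample follows: "For 50 newborns, the total number of HR annotations will be approximately 4500 data points".
- **Averaging.** Data Management: "The annotations from the 2 researchers will be averaged for the subsequent analyses". This combines two people's readings of the same time point. The 90 time points per infant stay separate.
- **Tests.** Data Analysis plans a t test for the mean difference: "The HR from HRD will be compared to PO or ECG using a paired" (the quote stops just before the test is named). For agreement it says: "The Bland-Altman method will be used to compare the HR derived from each device". For correlation it names Pearson r.
- **Data used.** Data Analysis: "Data will be first analyzed using all data points available". The same sentence defines an outlier by a 20 bpm difference between methods.

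The article mentions no clustering by infant, autocorrelation, mixed model, infant-level summary or repeated-measures form of Bland-Altman. It also states no significance level, confidence interval, ICC or success threshold.

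**The concern.** The independent unit is the infant. Readings 2 seconds apart in one infant share one placement of the heart rate detector (HRD), held by hand for a single 3-minute episode, and the same reference monitor. Study Procedures itself says that pulse oximetry and ECG, with their different sensing and algorithms, may display different rates. An offset tied to the monitor is then common to all readings of that infant. Displayed rates so close in time can also be expected to be serially correlated.

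The ordinary paired t test, the basic Bland-Altman standard errors and the usual inference for Pearson r assume one independent pair per row. Run on 4500 rows, they treat 90 related readings as 90 separate pieces of evidence. This bears on the research question about accuracy against pulse oximetry or ECG. The t test could report a difference between devices where there is no average bias, and any interval given for the bias or the limits of agreement would overstate what 50 infants can show.

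**Working it through.** **The plan's own figure.** 3 min = 180 s; 180 / 2 = 90 readings per infant per device; 50 × 90 = 4500. The stated total reproduces exactly.

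**Inputs.** From the article: 50 infants and m = 90 readings each. Assumed, because the article gives neither: the ICC of the HRD-minus-reference differences (shown as a range) and a two-sided nominal level of 5%.

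**Formulas.**
- Design effect: DE = 1 + (m − 1) × ICC = 1 + 89 × ICC
- Effective number of readings: 4500 / DE
- Factor by which the naive standard error is too small: √DE
- True type I error of the nominal 5% test: 2 × [1 − Φ(1.96 / √DE)]

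Example at ICC 0.1: DE = 1 + 89 × 0.1 = 9.9; √9.9 = 3.15; 1.96 / 3.15 = 0.62; 2 × [1 − Φ(0.62)] ≈ 0.53.

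| Assumed ICC | DE | Effective n | SE too small by | True type I error | Actual coverage of nominal 95% CI for bias |
|---|---|---|---|---|---|
| 0.01 | 1.89 | 2381 | 1.37 | 15% | 85% |
| 0.05 | 5.45 | 826 | 2.33 | 40% | 60% |
| 0.1 | 9.9 | 455 | 3.15 | 53% | 47% |
| 0.3 | 27.7 | 162 | 5.26 | 71% | 29% |
| 0.5 | 45.5 | 99 | 6.75 | 77% | 23% |

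**Simulation check** (2000 runs per setting, 50 infants × 90 readings, true bias zero):

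| ICC | Lag-1 autocorrelation | Pooled t test rejects | t test on 50 infant means rejects | Coverage of naive 95% CI for a limit of agreement |
|---|---|---|---|---|
| 0 | 0 | 5.1% | 4.6% | 94.5% |
| 0.05 | 0 | 43% | 5.9% | 74% |
| 0.1 | 0 | 52% | 4.7% | 64% |
| 0.3 | 0 | 71% | 5.2% | 40% |
| 0.5 | 0 | 79% | 5.8% | 26% |
| 0 | 0.8 | 49% | 5.0% | 56% |
| 0 | 0.9 | 63% | 4.0% | 43% |

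Of the settings simulated, the pooled analysis behaves properly only with no infant effect and no autocorrelation. Serial correlation alone is enough to spoil it.

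**Pearson r.** For an assumed r = 0.90, Fisher's transformation with standard error 1/√(n − 3) gives 0.894 to 0.905 at n = 4500 and 0.829 to 0.942 at n = 50. These mark the two ends: every reading independent, and only the infants counting. Pooled r has a further problem that no interval repairs. It mixes the association between infants' average rates with the tracking of changes within an infant.

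**What is little affected.** With equal readings per infant, the pooled mean difference equals the mean of the infant means, and the estimated limits of agreement change little.

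**The case against.** The article never says that readings will be treated as independent; that is inferred from the named methods and the stated data. The sentence about using all data points also deals with outliers, and may mean only that nothing is removed at first. Bland-Altman is a family that includes repeated-measures versions, and the variant could be left to a fuller plan. These points soften the wording for Bland-Altman. They do not rescue the paired t test or Pearson r. Averaging stops at the annotators, so the analysed row is still the single reading. The article does not merely leave out a detail: the unit and the tests it does state give a wrong p-value together.

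A reader might infer more than the article supports:

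- **That 4500 is claimed as the sample size.** It is given as a count of annotations. The Abstract and Recruitment both give the sample as 50 newborns.
- **That the planned confidence intervals are wrong.** None is planned. Only the t test necessarily yields a p-value; the rest applies if such results are reported.
- **That the feasibility conclusion as a whole rests on false precision.** Of the four questions under Objectives, placement time, ability to detect and speed are untouched. There is no success threshold, and the point estimates of bias and limits largely stand. The inflated t test also errs towards declaring a difference, which does not favour the device.

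It is also true that every size given here depends on an assumed ICC or autocorrelation.

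**Conclusion.** The concern holds in a bounded form. Followed as written, the plan gives an invalid p-value for the paired t test, and any p-value for r or interval for the bias, the limits of agreement or r taken from the pooled readings would be too small or too narrow. The direction is firm unless readings within an infant are uncorrelated, which one placement read every 2 seconds makes implausible. The size is conditional: about 15% to 77% true type I error for assumed ICCs of 0.01 to 0.5, against 4% to 6% for a test on infant means in the simulations. The damage is to inference in the accuracy comparison, and to the meaning of pooled r. It does not reach the main Bland-Altman point estimates or the other three research questions.

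**What to change.** In Data Analysis, state that the infant is the unit of inference, and then:

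- Replace the pooled paired t test with a test on the 50 infant mean differences, or a mixed model of the differences with a random infant effect that allows for serial correlation. The simpler option already restores the error rate.
- Use Bland-Altman limits for repeated measures, built from the between-infant plus within-infant variance.
- Report an infant-level or a within-infant correlation, and say which.
- Take any confidence intervals from a cluster-based method, such as a bootstrap that resamples infants.

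The cost is a change of wording and a little more analysis work. Recruitment, recording and annotation stay as they are. Reported intervals will be wider.
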